**9) Scintigraphic analysis: **Planar imaging of the lungs in anterior and posterior position will be performed 30 min, 90 min and 24 hours after the administration. At 24 hours single photon emission tomography (SPECT) imaging of the lungs will be also done. Imaging will be implemented in a single-head gamma-camera (GE Millennium MPS, Milwaukee USA) equipped with a low energy high resolution (LEHR) parallel-hole collimator. For planar imaging the matrix size will be set at 256 × 256, while for SPECT at 128 × 128 pixels; the photopeak will be centered at 140 keV, with a symmetrical 20% window. The tomographic imaging parameters consisted of a 360°-rotation angle, a circular technique and an acquisition time of 30 sec per frame. Raw imaging data will be reconstructed using the Butterworth-filtered back-projection algorithm, generating tomographic views of the lungs in the 3 planes (transverse, coronal, and sagittal). In order to estimate the retention of the radiolabeled cells in the lung in comparison to free technetium we will draw regions of interest (ROI's) over the right and left lung in the posterior images at 30, 90 min and 24 hours (Figure 2).

**10) Patient's discharge: **The patient will be discharged 24 hours post-bronchoscopy given that he/she is afebrile and hemodynamically stable, with no signs of infection or any type of allergic reaction.

**11) Clinical, functional and radiological assessment: **Arterial blood gases (ABGs) coupled with clinical (Borg and Medical Research Council-MRC dyspnea scales), health-related quality of life (Saint George's Research Questionnaire-SGRQ and cough assessment test-CAT) and functional (6-minute walking test-MWT, FVC and DL_CO_) assessment will be performed every month after the first infusion until the end of the follow-up period (12 months) and HRCT evaluation 6 months after the first infusion in order to estimate any potential clinical, functional and radiological differences compared to baseline modalities (Table 1).

**Table 1 T1:** Scheduled visits following endobronchial infusion of ADScs

No of Visit	Time-point (days)	ADSCs infusion	Physical Examination	Routine Laboratory tests	MRC dyspnea scale	SGRQ + CAT	6MWT	PFTs	ABGs	HRCT
1	0	1^st^	X	X	X	X	X	X	X	X
2	30	2^nd^	X	X	X	X	X	X	X	
3	60	3^rd^	X	X	X	X	X	X	X	
4	90		X	X	X	X	X	X	X	
5	180		X	X	X	X	X	X	X	X
6	270		X	X	X	X	X	X	X	
7	360		X	X	X	X	X	X	X	X + whole body HRCT scan

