### Primary end-points (Safety and Toxicity levels)

The procedure is safe and well tolerated by the patients, as reflected by the absence of signs compatible with infection, allergic reaction, disease acute exacerbation, and ectopic tissue formation, at 12 months after the first post-endobronchial infusion of SVF cells (total follow-up duration for each patients = 12 months).

In particular, patients will be subdivided into three categories depending on the level of toxicity, defined as:

**1) Low level**, including minor side effects such as increased cough, low fever (less than 37.5°C, skin allergic reactions)

**2) Medium level**, including non-life threatening allergic reactions, infections that do not require hospitalization, elevation of liver enzymes or creatinine serum levels.

**3) High level**, including death and/or life threatening major adverse events such as disease acute exacerbations defined as follows:

*a) *If the patient experiences a significant worsening of dyspnea and a decline in exercise tolerance associated with a 10% decrement of their FVC, a 10 mmHg change in PaO_2 _or 50% increase in their oxygen requirement, and a significant progression in their radiographic score between the three month clinic visits;

*b) *If the patient needs to be admitted to the hospital because of worsening respiratory failure requiring mechanical ventilation, worsening gas exchange, or presumed pulmonary infection.

*c) *If the patient develops ectopic tissue formation compatible with carcinogenesis as assessed by whole body computed tomography at 12 months after the first post-endobronchial infusion of SVF cells

Exploratory secondary end-points:

1) Assessment of Forced Vital Capacity (FVC%) predicted.

2) Assessment of Diffuse Lung Capacity for carbon monoxide (DL_CO_%) predicted.

3) Assessment of 6MWT.

4) Assessment of dyspnea scales (Borg, MRC) as well as health-related quality of life questionnaires (SGRQ)

5) Assessment of the disease extent and severity as reflected by chest high resolution computed tomography (HRCT) at 6 and 12 months post-bronchoscopy.

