*HRCT (scoring grade 0 = no lesion, grade 1 = less than 5% of the lobe, grade 2: 6-25% of the lobe, grade 3: 26-50% of the lobe, grade 4 = 51-75% of the lobe, grade 5 = 76-100% of the lobe). The "ground-glass" alveolitis will be defined as increased opacification of the lung without obscuration of the bronchial and vascular markings, whereas the fibrosis score will include thickening of the alveolar septa and subpleural areas of honeycombing.

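### Limb (a) of the acute-exacerbation definition needs radiographic progression between three-month visits, but no three-month interval has a scheduled HRCT at both ends, so it cannot be assessed as worded from scheduled imaging

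*Protocol article*

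**What the plan says.** In the section on primary end-points, the high toxicity level covers death and life-threatening events, among them acute exacerbation. Limb (a) asks for worse dyspnea and reduced exercise tolerance, together with one of three functional changes (FVC, PaO2 or oxygen requirement), and in addition "a significant progression in their radiographic score between the three month clinic visits". The PaO2 element reads "a 10 mmHg change in" PaO2, with no direction. Limb (b) is hospital admission for respiratory worsening or presumed pulmonary infection and needs no imaging.

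The imaging schedule appears in three places:

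- Study Methodology, item 11, names "HRCT evaluation 6 months after the first infusion", to be compared with baseline.
- Table 1 ("Scheduled visits following endobronchial infusion of ADScs") marks HRCT at days 0, 180 and 360. The day-360 cell reads "X + whole body HRCT scan". The HRCT cells at days 30, 60, 90 and 270 are blank.
- Exploratory secondary end-point 5 names HRCT at 6 and 12 months.

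The only imaging score defined is the lobe-extent grade that begins "HRCT (scoring grade 0 = no lesion, grade 1 = less than 5% of the lobe".

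**The concern.** Limb (a) is a conjunction, so a patient without the radiographic element does not satisfy it, however clear the clinical and functional decline. The definition ties that element to an interval of about three months, while the scans are six months apart.

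The mismatch concerns a component of the primary end-point in a 12-patient safety study. It can err in one direction only: a missing scan can prevent an event from being counted but cannot create one. The high toxicity level is also a ground for terminating the study (Study Duration & Termination), so the same definition may bear on that rule.

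**Working it through.** The plan gives no figure to reproduce here. The check sets the visit schedule against the imaging schedule.

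**Inputs (Table 1).** Visits: days 0, 30, 60, 90, 180, 270, 360. HRCT: days 0, 180, 360. MRC dyspnea scale, 6MWT, pulmonary function tests and arterial blood gases: every visit.

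**Step 1: is the radiographic element mandatory?** In limb (a) the word 'or' joins only the FVC, PaO2 and oxygen alternatives. The radiographic element follows with 'and'. No alternative is given for a visit without a scan.

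**Step 2: which visits are three months apart?** Taking all visit pairs with a difference of 90 days:

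| Interval (days) | HRCT at start | HRCT at end | HRCT at both | Lung function and blood gases at both |
|---|---|---|---|---|
| 0-90 | yes | no | no | yes |
| 90-180 | no | yes | no | yes |
| 180-270 | yes | no | no | yes |
| 270-360 | no | yes | no | yes |

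HRCT at both ends: 0 of 4. Lung function and blood gases at both ends: 4 of 4. The radiographic criterion is therefore the one that lacks data.

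**Step 3: does the other stated visit schedule change this?** Item 11 describes monthly assessments up to 12 months. Monthly visits add possible 90-day pairs (for example 30-120), but HRCT stays at days 0, 180 and 360. The gaps between consecutive scans are 180 - 0 = 180 and 360 - 180 = 180 days, so no 90-day pair can have HRCT at both ends.

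**Step 4: what if the definition follows the scans?** If progression is judged between scheduled HRCTs, the intervals are 0-180 and 180-360, and 2 of 2 are assessable without further imaging.

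**Step 5: the PaO2 wording.** FVC has a direction (a decrement) and so does oxygen requirement (an increase). PaO2 has only a change, so a rise of 10 mmHg would satisfy that element if read literally.

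**The case against.** A reader might infer that limb (a) can never be met and that the study must return zero such events. The documents do not support that. Table 1 lists scheduled visits, and nothing in the article bars an unscheduled scan when a patient deteriorates. Rules for event-driven imaging are detail that a condensed article may leave to the full protocol. A lenient assessor could also use the change since the last HRCT, although that departs from the wording.

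A reader might also infer that only hospital admission can register an exacerbation. That is too strong as well. Death is high level in its own right. Limb (b) covers several kinds of admission without imaging. The headline end-point is worded more broadly, as absence of signs compatible with exacerbation. What remains exposed is the patient who worsens but is neither admitted nor dies. That group may be small, given that the category is meant for life-threatening events.

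It is tempting to link the mismatch to the preliminary report of no clinically significant exacerbations (Discussion). Nothing shows that limb (a) produced that result, or that any patient met the other criteria without imaging.

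Nor does an exact interval measure the defect. One missed event would turn 1/12 (8.3%, exact 95% CI 0.2% to 38.5%) into 0/12 (upper limit 26.5%), but that is true of any missed event in any 12-patient study. The documents give no rate of exacerbation without admission.

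On PaO2, the surrounding sentence already requires worse dyspnea and reduced exercise tolerance, so the intended direction is fairly clear. The point is minor.

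After all this the contradiction stands. The article states both the interval and the scan days, and they do not fit, so condensation does not explain it.

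**Conclusion.** Wrong as written. Limb (a) cannot be assessed as worded from the scheduled imaging: 0 of 4 three-month intervals have an HRCT at both ends. The consequence is possible under-counting of exacerbations that lead to neither admission nor death, with a bias towards 'safe' in the primary result. The size of that bias cannot be estimated from the documents.

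The conclusion rests on two readings: that the radiographic score means the HRCT grade, the only score defined, and that the three-month clinic visits are visits about 90 days apart. It does not depend on the sample size, the significance level or the choice between the monthly and the Table 1 visit schedule.

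**What to change.** Reconcile the definition in the primary end-points section with item 11 and Table 1:

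1. Word the radiographic element of limb (a) as progression against the most recent earlier HRCT. The scheduled pairs are days 0-180 and 180-360; an unscheduled scan is used if one was done.
2. List separately, outside the primary count, patients who meet the dyspnea, exercise and FVC/PaO2/oxygen criteria at a visit without a paired HRCT. Adding them to the primary count would mix chronic progression with acute exacerbation in an uncontrolled study.
3. As a minor correction, change the PaO2 criterion from a change to a decrease, in line with the directions already given for FVC and oxygen requirement.

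Which events feed the termination rule is for the sponsor to reconcile.

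The cost is one reworded definition and one extra table row, with no added scans. The downside is that a 180-day comparison is less specific for an acute event, and some of the listed unpaired cases will be chronic progression.

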### Statistical analysis

Statistical analysis will be performed using the SPSS 16.0 software. Safety and exploratory efficacy secondary end-points will be observed for each patient against the baseline values. A p value < 0.05 will be considered as statistically significant.

### Basic Principles & Ethical Considerations

The study will be performed in accordance with Institutional Review Board and the Ethics and Scientific Committee of the University Hospital of Alexandroupolis, Democritus University of Thrace standards. Original protocol has already been approved by the Local Ethics and Scientific Committee of the University Hospital of Alexandroupolis, Democritus University of Thrace, Greece (reference number EHD33/1SC/16-02-2010)

Study Duration & Termination

The clinical part of the study will start after the approval of the responsible Ethics Committee and the study initiation visit is performed.

The time frame of the study will be as follows:

• Total Clinical Duration: 24 months

• Recruitment Period of Phase Ib (12 subjects): 12 months

• Treatment + follow-up (per subject): 12 months

The entire study may be prematurely terminated/discontinued if there is:

1. Comprehensive deficiency in the recorded data or protocol compliance so that the study cannot be reliably assessed

2. Occurrence of undesired experiences or adverse events necessitating termination (high toxicity level).

3. The Principal Investigator and the Project Manager commonly decide premature termination, after consultation with the Ethics Committee.

In the event of early termination, Investigator will cease use of the investigational drug immediately. A written statement fully documenting the reasons for such a termination will be provided from the Department of Pneumonology, Democritus University of Thrace to the Institutional Review Boards/Independent Ethics and Scientific Commitees and Regulatory Authorities of the University Hospital of Alexandroupolis, Democritus University of Thrace, Greece.

### Completed

The subject completes the study as per protocol at 12 months follow up after the first infusion of SVF cells and a whole-body CT scan will be performed at the end of the follow-up period to estimate the presence or not of ectopic tissue formation.

### Discontinued/withdrawn

Withdrawal from the study can occur under the following circumstances:

1. Death

2. Intolerable toxicity during infusion of test drug

3. Subject consent withdrawal

4. Investigator's discretion

5. Screening errors: From an analysis perspective, a 'screening error' is any subject who was enrolled into the study, e.g. was attributed a CRF with subject number, but was withdrawn (before or after randomization) prior to administration of IP for reasons such as protocol violation (inclusion/exclusion criteria) or withdrawal of consent.

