### Patients and methods

In our phase Ib dose escalating study will participate 12 with IPF, respectively, based on the recently published diagnostic criteria of ATS/ERS (2011), of mild to moderate disease severity as estimated functional parameters including forced vital capacity (FVC) > 50% and diffusing lung capacity for carbon monoxide (DL_CO_) > 35% of the predicted normal values. All patients will sign an informed consent form where they will agree to their participation in the study and the anonymous usage of their biological fluids for research purposes (see inclusion criteria below).

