**4) Lipoaspiration and isolation of ADSCs-SVF: **All eligible patients will undergo lipoaspiration under general anesthesia in a sterile surgical operating room setting. 50 mL of blood in EDTA will be taken to prepare platelet rich plasma (PRP). Approximately 100 - 500 gr of adipose tissue will be isolated from the above procedure performed by a plastic surgeon. Enzyme dissolution procedure of the adipose tissue, using collagenase type I solution under agitation for 2 hours plus 10 cc of lecithine followed by two centrifugations at 100 g for 10 minutes the first and at 1800 g for 10 minutes the second, will be performed to separate the stromal cell fraction (pellet) from adipocytes. The pellets will be treated with red lysis buffer. The final pellet will be re-suspended and a small volume of suspension will be used for flow cytometry analysis, counting CD29, CD73, CD90, CD34, CD105, positive cells and CD14, CD31 and CD45 negative cells in Coulter Epics XL/MCL. 10 mL of the suspension will be used for bacterial check with the BacT/Alert system (with colorimetric carbon dioxide detector). In the case of an infected sample the microorganism will be identified with VITEK 2 Compact 15 and will be excluded. A volume of DMSO solution will be added in the remaining suspension so that the final volume contains 10% DMSO and 2% Haes-steril 200. The cells will be cryo-preserved gradually and stored in cryovials, air-tightly sealed with cryoflex membrane. The vials will be placed in constant temperature in liquid nitrogen and will be stored there. Viability of the cells will be estimated by tryphan blue. A total of 3-5 × 10^6 ^cells per gram of adipose tissue is expected to be isolated. Based on the current literature [29], since SVF represents an heterogeneous cell population it is anticipated that approximately 50-70% of the total number of isolated cells to be of mesenchymal origin meaning CD29, CD105, CD90, CD73 positive and CD34, CD45 negative cells and 20-30% mature endothelial (CD31 and positive) and hematopoetic (CD34 positive) cells.

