### Recording Subject Withdrawals

In the event of a subject withdrawal, the following information must be recorded in the Case Report Form (CRF):

1. Date of withdrawal

2. Reason for terminating participation in the study

3. Last treatment date

4. Follow-up assessments

The Investigator should continue to follow-up all serious adverse events or other adverse events that are considered to be related to the study drug, until they are resolved or assessed to be chronic or stable by the Investigator. This should be documented in the subject's medical records. This follow-up may be extended beyond the end of the study period.

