### Replacement of Subjects Withdrawn

Subjects who are prematurely withdrawn from the study will not be replaced.

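### The primary safety window opens at the first infusion, so harvest harms fall before it, and withdrawal from the study for infusion toxicity leaves the 12-month assessments unassured

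*Protocol article*

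**What the plan says.** All references are to the Protocol article.

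- **Window.** Primary end-points (Safety and Toxicity levels) judges safety by the absence of infection, allergic reaction, acute exacerbation and ectopic tissue, "at 12 months after the first post-endobronchial infusion of SVF cells (total follow-up duration for each patients = 12 months". Table 1 places day 0 at the first infusion, and the section Completed counts 12 months from the same point.
- **Harvest.** Study Methodology, step 4: "All eligible patients will undergo lipoaspiration under general anesthesia in a sterile surgical operating room setting". This precedes randomization (step 6) and infusion (step 8).
- **Screening errors.** Discontinued/withdrawn, item 5, defines these from an analysis point of view. A screening error "is any subject who was enrolled into the study, e.g. was attributed a CRF with subject number, but was withdrawn" before receiving the investigational product, whether or not already randomized. The two reasons given as examples are a protocol violation and withdrawn consent.
- **Toxicity.** The same list gives "Intolerable toxicity during infusion of test drug" as a circumstance in which a patient may be withdrawn from the study.
- **After withdrawal.** Recording Subject Withdrawals requires the date, the reason, the last treatment date and follow-up assessments in the CRF. The investigator "should continue to follow-up all serious adverse events or other adverse events that are considered to be related to the study drug", until these resolve or become chronic or stable.
- **Replacement.** "Subjects who are prematurely withdrawn from the study will not be replaced".

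**The concern.** Safety and tolerability are the primary question, and the aim adds feasibility. The cells are autologous, so no patient can be infused without first being harvested. An infection or exacerbation between the two steps is the kind of event the endpoint lists, but it happens before the clock starts. A patient who is harvested and never infused may be set aside as a screening error, and a failure of feasibility goes with that patient.

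The second gap comes later. The article describes no status in which a patient stops infusions but stays under observation. A patient who leaves for toxicity may therefore have no 12-month scan and no later scheduled visits. The missing information would be concentrated in those who fared worst. Both gaps can move the result only towards 'safe'.

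**Working it through.** The point is mainly structural, so the passages are set side by side first. The article gives no event rate or precision target behind its 12 patients, so there is no stated figure to reproduce.

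**1. Order of steps against the window.** Lipoaspiration is step 4, randomization step 6 and infusion step 8. The window opens at the first infusion. Anything between steps 4 and 8 is outside it. None of the toxicity levels names a complication of harvest or anaesthesia.

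**2. Reach of the screening-error class.** It covers withdrawal before the product is given, including after randomization. In the listed order, anyone withdrawn after randomization has already been harvested, so the class does reach harvested patients. That it takes in patients *harmed* by harvest is an inference: the listed reasons are examples, and harm is not one of them.

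**3. What is lost after withdrawal for infusion toxicity.** Table 1 has visits at days 0, 30, 60, 90, 180, 270 and 360, with infusions at the first three. The later visits no longer assured are:

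| Withdrawn at | Visits left in Table 1 | Count |
|---|---|---|
| Infusion 1 (day 0) | 30, 60, 90, 180, 270, 360 | 6 |
| Infusion 2 (day 30) | 60, 90, 180, 270, 360 | 5 |
| Infusion 3 (day 60) | 90, 180, 270, 360 | 4 |

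The day-360 whole-body scan is lost in every row. Two parts of the high toxicity level depend on these visits. Ectopic tissue is assessed by that scan. The first exacerbation definition needs a change in FVC, PaO2 or oxygen requirement, plus radiographic progression between clinic visits. Follow-up of serious or related adverse events does not supply either.

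**4. Size.** Inputs: n = 12 (Patients and methods) and an assumed one harmed patient. The exact (Clopper-Pearson) 95% limits for x events in n are the 2.5% quantile of Beta(x, n − x + 1) and the 97.5% quantile of Beta(x + 1, n − x). For x = 0 the lower limit is 0 and the upper limit is 1 − 0.025^(1/n).

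- Weight of one patient: 1/12 = 8.3 percentage points.
- Harmed, never infused, left out: 0/11. Upper limit 1 − 0.025^(1/11) = 28.5%.
- Harmed before the window, infused later, event not counted: 0/12. Upper limit 1 − 0.025^(1/12) = 26.5%.
- Event counted: 1/12 = 8.3%, interval 0.2% to 38.5%.

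**The case against.** The strongest reply is that the stated hypothesis concerns the endobronchial infusion, so a clock that starts there matches the aim and is no contradiction. It adds that both named reasons for a screening error are administrative, that every withdrawal is recorded with its reason, and that analysis sets may be defined in a full protocol or analysis plan not shown. Much of this stands. Pre-infusion failures stay visible in the CRF, and without replacement they show against the planned 12. What it does not answer is that the article itself fixes the endpoint's start and defines the screening-error class for analysis. Followed as written, harvest harms do not enter the primary result.

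Two stronger readings are tempting and should not be made.

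- A reader might infer that infused patients withdrawn for toxicity leave the primary endpoint altogether. No sentence says so. Death is both a withdrawal reason and high-level toxicity, so the plan treats withdrawal and grading as compatible. The triggering event falls inside the window and can be graded. Subtracting such patients from the denominator has no basis in the text.
- A reader might take the endpoint as status at month 12 only, so that an infection resolved earlier would not count. The preposition is loose, but the toxicity levels list transient events such as cough and low fever, the same sentence gives a 12-month follow-up, and the Discussion reports events cumulatively. The wording deserves tidying; it is not an error in the rule.

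**Conclusion.** The point holds in two parts. First, harms of a mandatory surgical step precede the primary safety window, and a harvested patient who is never infused can be classed out of the analysis. Second, when infusion toxicity leads to withdrawal from the study, the later visits and the 12-month scan are not assured, so late exacerbation and ectopic tissue may go unobserved in those patients.

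One affected patient shifts the observed rate from 0 to 8.3%. That count is assumed; the Discussion reports no clinically significant infections, allergic reactions or exacerbations among the 12 enrolled, and nothing here suggests otherwise. The first part assumes that the screening-error class is applied to any withdrawal before infusion. The second assumes that the permissive withdrawal rule is used and that scheduled visits then cease, which the text neither states nor prevents.

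**What to change.** Change the wording in four places. When infusions should stop is a clinical matter and is left as it is.

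1. **Endpoint.** Count the listed events occurring at any time from the start of lipoaspiration through 12 months after the first infusion, or through 12 months after harvest for a patient never infused.
2. **Population.** Report safety and feasibility for all patients who start lipoaspiration. Limit 'screening error' to withdrawals before it. Events before and after the first infusion can be shown separately, so that the infusion question is still answered.
3. **Withdrawal.** Separate stopping infusions from leaving the study. Patients who stop infusions keep the planned visits and the day-360 whole-body CT unless they withdraw consent.
4. **Missing scans.** Report patients without the 12-month scan as not assessed for ectopic tissue, not as event-free. An earlier scan at exit would not replace the 12-month assessment.

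The cost is protocol and CRF wording, and visits that continue for patients no longer being infused; the visits and the scan are already scheduled, except that a patient never infused needs follow-up timed from harvest. The reported event rate may be less favourable. Since the Discussion describes 12 patients already enrolled, the changes would apply to whatever follow-up remains and to how the results are reported.
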